### Sample size

We will aim to recruit *N* = 60 participants (30 per trial arm). This number will enable key outcomes of interest, linked to our progression criteria, such as retention rates, and key parameters to inform a power calculation for a larger trial, such as the standard deviation of clinical outcome measures, to be estimated with adequate precision and minimal bias [56, 57]. For example, Teare and colleagues [56] recommend a sample of 60 or more based on simulation results for estimating event rates. Note that we are interested in event rates across both arms for our progression criteria (i.e. we are not evaluating progression criteria separately for each arm).

### Data management

Participant data will be stored confidentially and anonymised upon completion of the trial. Participant data will be stored securely either in locked cabinets at NHS sites or on secure, password-protected NHS computer drives. Identifiable information will be stored separately to other study data, using a linking code to connect the two types of data. Datasets will be designed to minimise data entry errors by having pre-specified admissible values. A 10% subset of data entry will be done independently, in parallel, to assess quality of data entry. Discrepancies will be reviewed and further parallel data entry undertaken where data entry problems are noted. A detailed study data management plan is available from the authors on request. Anonymised trial data will be made available to other researchers following publication of the main trial paper, via a suitable online repository.

### Statistical analysis

As this is a feasibility study, we will report descriptive data on study ‘processes’ and ‘outcomes’. An intention-to-treat (ITT) protocol will be followed. Descriptive data concerning recruitment, retention, and attrition will be presented in a CONSORT flow chart [58]. Treatment engagement and attrition rates will be calculated with associated confidence intervals and reasons for leaving the trial or therapy early will be reported where available. Rates of missing data will be presented for outcome measures. Descriptive statistics will be presented for the overall sample and by group for all potential outcome measures. RELATE-YP is a feasibility study and inferential testing of treatment efficacy is therefore not the goal of the study. Nonetheless, we will estimate treatment effects and associated confidence intervals to inform planning for a future trial. These analyses will use an appropriate regression model, depending on the distribution of the outcome variable (e.g. linear regression for continuous outcomes, negative binomial regression for count outcomes). A detailed SAP will be drafted by the trial statistician and approved by the TSC prior to any analyses taking place. This will be available from the research team on request. No interim analyses are planned. Imputation may be used to generate total scores on scales where < 20% of items are missing but will not otherwise be used.

For the feasibility economic analysis, the extent of missing cost and outcomes data will be presented using descriptive statistics. The CHU9D will be used to derive quality-adjusted life years (QALYs), in line with National Institute for Health and Care Excellence (NICE) reference case [59]. The cost of delivering the intervention will be estimated based on the resources used as recorded by trial therapists. Published NHS and social care unit costs will be attached to these estimates of resource use. The identity and quantity of other health and social care resources used by participants will be captured and summarised. This information is required for a full economic evaluation and will be used to understand what services participants access as TAU to help define exemplar comparators for a future cost-effectiveness analysis. Data on what participants received as TAU will be presented in our final reporting and reviewed holistically to help inform the planning of a future definitive trial.

Each participant in the brief CAT arm will rate a range (1-3) of TPs and associated TPPs at each session, including the follow-up. Participants therefore will generate a time-series of sessional TP/TPP recognition and revision scores. To analyse changes in recognition and revision ratings, linear mixed-effects models will be used. Models will then be extended to include random slopes if this improves model fit. Follow-up session TP/TPP ratings will not be included in the mixed-effects model, because of the time interval between the final CAT session and the follow-up (i.e. 4 weeks). Trajectories of predicted revision and recognition TP/TPP scores will also be plotted. A more detailed analysis plan with be pre-registered prior to undertaking these analyses.

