### Primary outcomes

The primary trial outcomes relate to feasibility and acceptability. Data on recruitment rates, participant retention at follow-up assessments, missing data, and adherence (i.e. attendance at therapy sessions) will be recorded and evaluated against a set of pre-specified progression criteria (see Table 1). These criteria will indicate whether progression to a definitive trial is warranted, using a traffic light system (green = progress to larger trial; amber = modification needed; red = do not progress). Acceptability will also be evaluated via the qualitative process analysis. Levels of missing data and qualitative data will guide decisions about the most appropriate primary outcome for an efficacy trial. It is anticipated that self-harm urges, assessed via the Alexian Brothers Urges to Self-Injure scale (ABUSI; [34]), or behaviour, assessed via the Self-Injurious Thoughts and Behaviours Interview Short Form (SITBI; [28]), would be the primary outcome in a subsequent trial. However, the suitability of these outcomes would be evaluated based on statistical considerations and participant feedback plus guidance from the Patient and Public Involvement (PPI) advisory group.

**Table 1 Tab1:** Progression criteria

Outcome	Criterion	Green	Amber	Red
Recruitment	Ability to randomise 60 participants in a 12-month recruitment window	≥ 80%	60%—79%	< 60%
Retention	Percentage of participants attending the 16-week assessment as the potential primary outcome timepoint	≥ 75%	60%—74%	< 60%
Outcome Suitability	Missing data on candidate primary outcomes (SITBI, ABUSI) at 16-week assessment	≤ 15%	16%—25%	> 25%
Adherence	Percentage of participants receiving the minimum dose of therapy (≥ 4 sessions) within 16-week treatment window	≥ 75%	60%—74%	< 60%

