#### Self-harm behaviour and urges

The SITBI short form [28] is a structured interview measure that will be used to assess suicide attempts and non-suicidal self-injury (NSSI). Sections of the measure will be adapted in line with the revised version of the SITBI [35] to improve the clarity of questions. Specifically, the opening question about NSSI will use the wording from the revised SITBI that provides additional detail on what might be considered as NSSI and some examples of behaviours that would not count as NSSI including indirect forms of harm (e.g. starving oneself). The ABUSI [34], a 5-item questionnaire, will be used to assess urges to self-harm over the past week. Scores range from 0 to 30 with higher scores indicating more severe urges. The validity and reliability of both measures have been demonstrated with young people [28, 34].

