#### Dependence on self-harm

The Experiences of Self-Injury Questionnaire—Positive Beliefs subscale (ESIQ; [36]) is an 8-item questionnaire that measures positive beliefs and perceived dependency on self-harm. Scores range from 0 to 32 with higher scores indicating greater dependency. Research has supported the factor structure, validity, and reliability of this measure [36].

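### The under-20% item-missingness rule can never apply to the 5-item ABUSI, so one blank item loses the total score of a candidate primary outcome

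*Protocol article*

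**What the plan says.** Four statements in the protocol article bear on this point.

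- **Statistical analysis** sets the rule for partly completed scales: "Imputation may be used to generate total scores on scales where < 20% of items are missing but will not otherwise be used". The inequality is strict, the last clause closes off any other imputation, and no exception is made for short scales.
- **Self-harm behaviour and urges** gives the length of the instrument, "The ABUSI [34], a 5-item questionnaire, will be used to assess urges to self-harm over the past week", and shows that it is used as a total: "Scores range from 0 to 30 with higher scores indicating more severe urges".
- **Primary outcomes** names the ABUSI, with the SITBI, as an anticipated primary outcome of the later trial. Table 1 has an Outcome Suitability row worded "Missing data on candidate primary outcomes (SITBI, ABUSI) at 16-week assessment", with green at ≤ 15%, amber at 16% to 25% and red above 25%. The same section adds: "Levels of missing data and qualitative data will guide decisions about the most appropriate primary outcome for an efficacy trial".
- **Data collection** says that researchers administer the measures and help the young person to answer where needed.

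**The concern.** A threshold for filling in blank items is meant to save a total when a respondent misses a little. On a five-item scale the smallest possible gap is one fifth, which is exactly the excluded boundary. The rule therefore works for the longer secondary questionnaires and fails for the one questionnaire among the two candidate primary outcomes, the SITBI being an interview.

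Two uses of the data are affected. First, the Sample size section relies on this trial for standard deviations to plan the definitive trial, and treatment effects with confidence intervals will be estimated. Each lost total removes a participant from both. Second, the completeness of the ABUSI is itself being judged. If missing data in Table 1 means a missing total, part of the figure will reflect the scoring rule and not only how much of the scale participants left blank.

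**Working it through.** **1. What the rule tolerates.** For a scale of k items, find the largest number of blanks m with m/k < 1/5, and then with m/k ≤ 1/5. Item counts come from the Clinical outcomes subsections.

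| Scale | Items | One blank | Max blanks, < 20% | Max blanks, ≤ 20% |
|---|---|---|---|---|
| ABUSI | 5 | 20.0% | 0 | 1 |
| ESIQ | 8 | 12.5% | 1 | 1 |
| PHQ-A | 9 | 11.1% | 1 | 1 |
| SDQ | 25 | 4.0% | 4 | 5 |

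This step needs no assumption. The ABUSI is the only one of the four that gets no relief.

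**2. Share of attended ABUSI totals lost.** The protocol gives no skip rate, so this step is illustrative. Assume each item is blank with probability q, independently of the others.

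- Current rule: 1 − (1 − q)^5
- With ≤ 20%: 1 − (1 − q)^5 − 5q(1 − q)^4

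The expected count uses 45 attenders. This is also an assumption: 75% of 60, the lower edge of green for retention.

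| q | Lost, current rule | Lost, ≤ 20% | Expected lost of 45, current | Expected lost of 45, ≤ 20% |
|---|---|---|---|---|
| 0.5% | 2.5% | 0.02% | 1.1 | 0.01 |
| 1% | 4.9% | 0.1% | 2.2 | 0.04 |
| 2% | 9.6% | 0.4% | 4.3 | 0.17 |
| 3% | 14.1% | 0.8% | 6.4 | 0.38 |
| 5% | 22.6% | 2.3% | 10.2 | 1.02 |

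For comparison, the nine-item PHQ-A at q = 2% loses 1 − 0.98^9 − 9 × 0.02 × 0.98^8 = 1.3% of totals under the current rule.

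**3. Effect on precision.** If totals are lost at random, confidence intervals widen by about 1/√(1 − share lost). At q = 2% this is 1/√0.904 = 1.05, and at q = 3% it is 1/√0.859 = 1.08. That is 5% and 8% wider, a modest loss.

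**4. Effect on the traffic light, on one reading only.** Suppose missing data means a missing total and the denominator is attenders. Of 45 attenders, green allows 6 missing totals (6/45 = 13.3%; 7/45 = 15.6%). From the binomial distribution, the chance of 7 or more from skipped items alone is 0.6%, 14%, 46% and 91% at q = 1%, 2%, 3% and 5%. At q = 0.5% it is negligible. With ≤ 20% it is at most about 0.01% throughout. The item rate whose expected loss equals the 15% limit is 1 − 0.85^(1/5) = 3.2%.

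**5. Sensitivity to independence.** At the other extreme, respondents who leave anything blank leave all five items blank. Then q = 2% loses 2% of totals instead of 9.6%, and the change to ≤ 20% recovers none of them.

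**The case against.** The boundary arithmetic is not open to dispute. The case on the other side concerns its consequences, and much of it stands.

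- **Progression.** A reader might infer that a skipped item necessarily counts against the progression criterion. Table 1 does not support that. It does not say whether missing data means totals, items or whole instruments, or whether the denominator is randomised participants or attenders. If items were counted, one blank would be a fifth of a score. If all 60 were the denominator, 45 attenders would already leave 15/60 = 25% missing, so attendance and not item skipping would have lost green.
- **Size.** Because a researcher administers the questionnaires, accidental blanks may be rare, and at q = 1% or below the effect on the rating is small. Blanks may also cluster on a short scale about one topic. The table in step 2 is therefore a range under an assumption and not a forecast.
- **Rejection of the ABUSI.** A reader might also infer that the rule could get the scale rejected. The text does not support this either. Amber means modification, and the choice of outcome also draws on statistical considerations, participant feedback and the PPI group. Rates of missing data will be reported, so the team could see that single items were the cause.
- **Strictness may be deliberate.** A blank item is incomplete data. Where missingness is a primary feasibility outcome, prorating before counting could hide the signal. This is a good reason to report raw completeness as well. It does not explain why the longer scales get relief and the ABUSI does not.
- **The SAP.** Scoring detail and the definition of missing data may sit there. But the article fixes the threshold and rules out imputation beyond it, so an SAP that allowed one blank ABUSI item would depart from the protocol.

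**Conclusion.** The point holds in a limited form. It is certain that, as written, one blank item removes the ABUSI total and that no partly completed ABUSI can benefit from the rule. It follows that the total is lost to the SD and treatment-effect estimates; the answers to the other four items are not said to be discarded. The effect on Outcome Suitability is conditional on reading Table 1 as counting missing totals.

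The practical size is unknown. Under independent skips of 0.5% to 3% it runs from about 2.5% to 14.1% of attended totals, against under 1% with ≤ 20%. It would be smaller, and less recoverable, if blanks cluster. With researcher-supported completion the lower part of that range is plausible. This is a cheap improvement to the plan and not a threat to the trial's conclusions.

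**What to change.** In the Statistical analysis section, and in the SAP to match, change < 20% to ≤ 20%. For the ABUSI this means at most one of five items blank, with the total prorated from the completed items. The ESIQ and PHQ-A still tolerate one blank item, and the SDQ goes from four to five.

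For the Outcome Suitability row of Table 1, state which level and denominator decide the rating. Report both the share of participants with all ABUSI items complete and the share with a computable total, so that prorating does not conceal incomplete responding.

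The cost is one character in the rule and one extra line in the report. The small downside is that a prorated ABUSI total rests on four items.

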### Qualitative process analysis

Qualitative data concerning acceptability of the intervention will be transcribed verbatim and analysed via framework analysis [60], which is useful for research with multi-disciplinary teams, clinicians, patients, and the public to evaluate trial delivery, implementation, and participant experience. We will follow the qualitative framework analysis approach [60, 61]. The steps of the analysis will comprise: (1) data familiarisation, (2) identifying a thematic framework by developing a coding scheme, (3) indexing all study data against the framework, (4) charting to summarise the indexed data, and (5) mapping and interpretation of patterns found within the charts. Members of the advisory group will be invited to contribute to the analysis and provided with training to enable this. Qualitative data regarding participant’s view on the acceptability of trial procedures more generally will be analysed using content analysis, generating themes based on shared ideas and perspectives. NVIVO software may be used to assist analysis [62]. Anonymised participant quotes will be presented as part of the results.

### Ethics

This trial is currently under review from an NHS research ethics committee (Greater Manchester Central; REC ID: 344,320). Any proposed modifications to the trial that require ethical amendments will be reviewed by the TSC and sponsor.

### Dissemination

Trial results will be disseminated through peer-reviewed journal articles and via presentations at national and international conferences. Press releases may be issued to coincide with the publication of results and to share the results of the trial amongst the general public. A variety of stakeholders including clinicians, young people, trial participants, parents and guardians, and researchers will be invited to a dissemination event once the trial is completed, where the results will be presented and discussed.

## Discussion

Self-harm can have a major impact upon a young person’s life, often being a source of substantial distress and a robust risk factor for later difficulties including further acts of self-harm. Given the increasing rates of self-harm amongst young people, it is clear that evidence-based psychological therapies are needed. Brief CAT has potential as a brief and structured relational therapy that may complement and add to existing treatment options for young people that self-harm. As a relational therapy, CAT differs to existing behavioural approaches like DBT and CBT, placing greater emphasis on interpersonal processes including the therapy relationship, and seeking to understand self-harm in terms of underlying relational patterns. Brief CAT may provide a helpful alternative, expanding service provision and enhancing patient choice. CAT has a developing evidence base in young people but clinical trials are needed to determine its efficacy as a treatment for difficulties like self-harm in young people [63, 64]. The RELATE-YP trial is therefore an important first step in evaluating brief CAT for young people who self-harm, and will answer important feasibility uncertainties, that in turn will inform the development of a larger, definitive trial. For example, data regarding recruitment rates and attrition will inform the required length and sample size of a future study, whilst qualitative data may lead to refinements to the therapy or trial procedures. The proposed feasibility trial, given its sample size, is not suitable for testing efficacy, but by paving the way for a larger definitive trial will help to inform clinical practice and guidance regarding treatments for self-harm in young people.

## Data Availability

An anonymised version of the final trial dataset will be made available to other researchers following publication of the study.
